# Mobile health technology, exercise adherence and optimal nutrition post rehabilitation among people with Parkinson’s Disease (mHEXANUT) – a randomized controlled trial protocol

**DOI:** 10.1186/s12883-023-03134-5

**Published:** 2023-03-02

**Keywords:** Parkinson’s Disease, Digital health, m-health, Exercise, Nutrition, Activity tracker

## Abstract

**Background:**

Although it is well known that regular physical activity and exercise, as well as maintaining adequate nutritional status is important to delaying symptom development and maintaining physical capacity and function in people with Parkinson’s Disease (PD), many are unable to follow self-management recommendations. Active interventions have shown short-term effects, but there is a need for interventions that facilitate self-management over the course of the disease. Until now, no studies have combined exercise and nutritional interventions with an individual self-management approach in PD. Thus, we aim to examine the effect of a six-month mobile health technology(m-health)-based follow-up programme, focusing on self-management in exercise and nutrition, after an in-service interdisciplinary rehabilitation programme.

**Methods:**

A single-blinded, two-group randomised controlled trial. Participants are Adults aged 40 or older, with idiopathic PD, Hoehn and Yahr 1–3, living at home. The intervention group receives a monthly, individualized, digital conversation with a PT, combined with use of an activity tracker. People at nutritional risk get additional digital-follow-up from a nutritional specialist. The control group receives usual care. The primary outcome is physical capacity, measured by 6-min walk test (6MWT). Secondary outcomes are nutritional status, Health related quality of life (HRQOL), physical function and exercise adherence. All measurements are performed at baseline, after 3 months and after 6 months. Sample size, based on primary outcome, is set at 100 participants randomized into the two arms, including an estimated 20% drop out.

**Discussion:**

The increasing prevalence of PD globally makes it even more important to develop evidence-based interventions that can increase motivation to stay active, promote adequate nutritional status and improve self-management in people with PD. The individually tailored digital follow-up programme, based on evidence-based practice, has the potential to promote evidence-based decision-making and to empower people with PD to implement exercise and optimal nutrition in their daily lives and, hopefully, increase adherence to exercise and nutritional recommendations.

**Trial registration:**

ClinicalTrials.gov (NCT04945876). First registration 01.03.2021.

**Supplementary Information:**

The online version contains supplementary material available at 10.1186/s12883-023-03134-5.

## Background

Parkinson’s disease (PD) is the fastest growing neurological disorder in the world [1]. It is a progressive and disabling disease with both motor and non-motor symptoms [2], potentially affecting several domains of a person’s life, including nutritional status [3, 4], health-related quality of life (HRQOL) [5], physical function and activity for daily living [6, 7].

It is known that physical activity and exercise can slow disease process and brain atrophy in PD, as well as delay symptom development [8], improve cognitive and physical function and capacity [9–12], and increase HRQOL [12–14]. Physical activity and exercise are closely related constructs but have different meanings, where the former is any bodily movement produced by the skeletal muscles resulting in energy expenditure, while the latter is intentional physical activity for improving health and fitness [15]. Due to the well-known effects of physical activity and exercise, they are key elements in today’s treatment guidelines and a combination of regular physical activity and exercise of moderate to high intensity is recommended [16]. Multiple forms of exercise are effective [8, 12, 17, 18], but have primarily short-term effect [19], and after a supervised exercise period, measures tend to return toward baseline values [12, 17, 20]. This regression may partly reflect the progressive nature of PD, but previous research suggests that maintaining motivation for exercise is difficult once formalised interventions end [20–24]. Experiences of poor health and disability symptoms may contribute to self-imposed activity restrictions and inactivity [25]. In addition, the experience of apathy, affecting the ability to initiate exercise, is a common non-motor symptom in PD [26]. Knowing the benefits of physical activity and exercise is not enough to change from a sedentary to an active lifestyle [27] and many people with PD remain sedentary [18, 28, 29].

Good nutritional status is an essential predictor of health status among people with PD [3], and unintentional weight loss is a commonly documented symptom [3, 30, 31]. Symptoms associated with PD [32] and pharmaceutical therapies used to alleviate PD symptoms [31] are both potential factors that can decrease food and energy intake, leading to weight loss. It has been reported that between 2 and 34% of people with PD— depending on population and measurement methods—are at risk of malnutrition [33, 34]. Malnutrition is associated with adverse outcomes such as increased mortality, hospitalisation, and reduced physical function [30]. Not having enough energy to fuel daily activity can lead to fatigue, decreased endurance and reduce overall physical function. Although previous studies have concluded that nutritional education can improve nutritional status in community-dwelling older adults [35, 36], there is limited research evidence on this topic in the PD population [37]. Nevertheless, the nutritional guidelines for people with PD focuses on early detection of nutritional problems, advice for common nutritional challenges and maintenance or improvement of physical function [38, 39]. In addition, optimal nutrition and dietary habits can positively affect the effectiveness of PD medications and potentially slow down disease development [40], as well as improve symptom management and overall well-being [39, 40].

Over the years, patients have been playing a greater role in managing their disease, and a key element of treatment is self-management [41–43]. Self-management refers to the different tasks an individual must take on in the day-to-day management of chronic conditions to live a decent life with the disease [44, 45]. Although previous research suggests that both exercise and nutrition should be part of long-term self-management in people with PD [3, 12, 42], adherence to self-management regimens tends to vary greatly [46, 47]. Research indicates that follow-up at home after rehabilitation is necessary to increase optimal nutrition and adherence to exercise [21, 48] and people with PD have identified self-management components as a research priority [49]. Consequently, the challenges for long-term self-management to recommendations are an important future concern for research and practice. To improve the management of PD in a community setting, people with PD, and their caregivers, have among other things expressed a desire for a person-and-community-centred approach, accessibility to support systems, information on health care services and a more comprehensive approach [50].

Several factors that can help increase adherence to nutrition and exercise recommendations among people with PD have been suggested [18, 47, 51]. Self-efficacy, an individual’s belief in their own ability to carry out an action successfully [23, 52], plays a key role in adherence to regular exercise [53]. Instructions and education are important, but not enough. Help to overcome barriers and identify motivators to engage in exercise is necessary [54], and both personal and environmental factors need to be addressed [55]. Wearable technology, such as activity trackers, is designed to motivate and offer support to individuals in self-monitoring and increasing their daily physical activity and exercise [56]. Such activity trackers can also monitor heart rate and exercise intensity [57], and thus facilitate a greater awareness of exercise at the recommended intensity level. They can promote physical activity among people with PD, though more research is necessary [58–63]. Further, social support is vital for many people with PD after rehabilitation [64–66] and physiotherapists (PTs) can play a crucial role in enabling people to improve their health, well-being and HQOL [67]. A large range of potential barriers and motivators for exercise in people with PD is found, and it is often experienced as difficult to achieve the recommended exercise dose outside clinical and research settings [54]. PTs are recognized as important in both identifying and addressing the person specific barriers and motivators, and through this, facilitate a better adherence to recommendations [54]. However, today, long-term PT follow-up among people with PD is often random or rare, despite being a priority [68].

Telehealth/m-health is found to be a potentially low-cost and efficient element within healthcare treatment programs [69, 70], and both patients and caregivers are generally positive to these forms of treatment [69–71]. This also includes people with PD who in one study responded that telehealth was convenient, easy to use, had the potential to give the same quality of follow-up care as in-person visits, and that telehealth could make follow-up easier in cases were traveling was problematic [71]. Even though the transition to more digital solutions was already established, the recent pandemic has accelerated the development of digital health care [71–74], increasing the relevance of these types of interventions. A monthly digital follow-up on physical activity, exercise, and nutrition, might make long-term follow-up more accessible and less time-consuming for individuals, potentially reducing costs to society [69] and hopefully improving long-term self-management in people with PD.

The combination of nutrition and exercise has been shown to improve health outcomes, and interventions combining both is found to have better effects than either one alone in other populations [75–77]. This combination has not yet been studied in the PD population, but it is suggested that it has the potential to slow down the progression of the disease [40]. A focus on self-management with a comprehensive approach is both desired [50, 78] and recommended for future research in this area [49, 79].

Based on current knowledge, we have designed a new m-health follow-up programme to improve self-management of nutrition and physical activity among people with PD after an in-service interdisciplinary rehabilitation programme at a rehabilitation centre in Norway. The follow-up programme includes a monthly, individualised digital conversation (video or telephone) on, e.g. motivation, exercise, nutrition, and other relevant areas, combined with the use of an activity tracker. People at nutritional risk will receive additional digital follow-up from a registered nurse (RN) specialised in nutrition. To our knowledge, no study has examined the effect of an m-health follow-up programme focusing on physical activity, exercise, nutritional status, and HRQOL among people with PD. Therefore, the objectives of this study are:

To examine the effect of an individualised, m-health follow-up programme focusing on self-management in physical activity, exercise, and nutrition on physical capacity among people with PD after attending an in-service interdisciplinary rehabilitation programme.Secondary objectives are to examine the effects of the m-health follow-up programme on nutritional status, HRQOL, physical function and exercise adherence.

## Methods

### Design

This is a single-blinded, two-group randomised controlled trial. Participants are recruited after attending a 4–5-week interdisciplinary rehabilitation programme at a rehabilitation centre. The intervention group will receive six-month of individually tailored m-health-based follow-up focusing on self-management of exercise and nutrition, and use of an activity tracker for motivation and monitoring activity levels. The control group will receive usual care, except for re-testing.

### Participants

Participants will be recruited during their elective admission stay at the rehabilitation centre. Eligible participants will be contacted by the research assistant (PT) and given oral and written information about the study. All participants will provide written informed consent before participating in the study. See Fig. 1 for planned flow of participants.

**Fig. 1 Fig1:**
[figure not shown]
Planned Flow of Participants

### Inclusion/exclusion criteria

Eligibility criteria were adults aged over 40 years, with a diagnosis of idiopathic PD and a Hoehn and Yahr stage of 1–3, living at home, within a maximum travel time of 2.5 h from the rehabilitation centre and in ownership of a smartphone.

The exclusion criteria were people with Hoehn and Yahr stage of 4–5 and medical issues that might affect participation in an exercise programme, as well as a dementia diagnose or severe dysphagia. People receiving enteral or parenteral nutrition and patients who, before admission to the rehabilitation centre exercised structured/planned, regularly more than twice weekly.

### Randomisation

The participants will be randomly assigned at a 1:1 ratio to the intervention or control group using a computer-generated, permuted block randomisation scheme, set up by an independent statistician before the trial. The PT responsible for the follow-up is getting the information on allocation on an ongoing basis from the principal investigator and informs the participants on which group they are allocated to after baseline testing, at the end of stay.

### Assessment and blinding

Baseline assessment will be conducted at the end of stay at the rehabilitation centre by a trained assessor. After three and six months (± one week), follow-up testing will be conducted at the rehabilitation centre by the same assessor. To increase accuracy, we will strive to conduct measurements at approximately the same time of day at baseline, three months, and six months. This to ensure that the participants are at the same medication level and in their on-phase, as this can affect function.

The assessor will be blinded to group allocation. Participants are asked not to share information on group allocation during assessments and, when applicable, to remove their activity tracker before meeting the assessor. Because of the nature of the intervention, we are unable to blind the treating therapist or the participants to group allocation. Participants are included at the end of stay so that they have limited opportunities to discuss their group allocation with other potential participants.

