### Interdisciplinary rehabilitation programme at the rehabilitation centre

All participants are recruited after attending a 4–5-week rehabilitation programme at a rehabilitation centre in Norway. This is an individualized comprehensive interdisciplinary rehabilitation programme with focus on self-management of the disease including exercise and nutrition, based on European guidelines for treatment of people with PD [42]. The participants receive education on relevant PD-related topics, such as medication, nutrition, and exercise, combined with group-based and individual follow-up on, e.g. exercise, speech and language therapy, medication, and nutrition. At the end of stay they receive recommendations from their team at the centre on a home-based rehabilitation plan, focusing on areas relevant to the individual patient, as aforementioned. In this plan, all are encouraged to engage in cardiovascular exercise combined with symptomatic exercise, e.g. Parkinson wellness recovery, which often includes strength exercises. See appendix 1 for a full description of the intervention at the rehabilitation centre.

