### Outcome measures

#### Baseline characteristics

At baseline, information about the participants health and sociodemographic variables, such as age, gender, living arrangements, education level, previous falls, home care services, physical activity level, degree and type of follow-up from PTs if any, medication list, comorbidities, and time of PD diagnosis, is assessed. Several of these variables will also be registered at follow-up to be able to assess changes in e.g. weekly exercise and medications. Food, diet habits and meal frequency are measured by the ‘*Hva Spiser Du?*’ (‘What do you eat?’) questionnaire. To assess the participants’ cognitive function, the Montreal Cognitive Assessment (MoCa) test is used, widely applied to screen for mild cognitive impairment and dementia and validated for the PD population [84, 85].

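### Testing at about the same time of day, as an aim only, cannot ensure the same medication level and on-phase at each 6MWT; on/off state can add noise of unknown size to the primary outcome

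*Protocol article*

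**What the plan says.** In the protocol article, Assessment and blinding sets one rule for medication state at testing: "we will strive to conduct measurements at approximately the same time of day at baseline, three months, and six months". The reason follows directly: "This to ensure that the participants are at the same medication level and in their on-phase, as this can affect function". So the article names a property that it needs, and it accepts that medication state changes function. The only means it gives is an approximate match on clock time, worded as an aim.

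The settings of the visits differ. For baseline: "Baseline assessment will be conducted at the end of stay at the rehabilitation centre by a trained assessor". For the later visits: "After three and six months (± one week), follow-up testing will be conducted at the rehabilitation centre by the same assessor". By then participants live at home, and eligibility allows homes "within a maximum travel time of 2.5 h from the rehabilitation centre".

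Medication is not treated as fixed. The residential programme includes "group-based and individual follow-up on, e.g. exercise, speech and language therapy, medication, and nutrition", and Baseline characteristics says of the medication list and other items: "Several of these variables will also be registered at follow-up to be able to assess changes in e.g. weekly exercise and medications".

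**The concern.** Time of day stands in for medication state only when a participant takes the same drugs at the same times on each test day. The article gives no ground for assuming this from the end of a residential stay to visits three and six months later, and its own plan to assess medication changes allows for the opposite. If intake times or regimen have moved, a test at the same hour can be taken in a different state, with the rule fully obeyed.

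The outcome at stake is the 6MWT, which is primary. A test taken off rather than on would record a shorter walk for a reason other than physical capacity. If this happens equally often in both arms, it adds variance and costs power. If it happens more often in one arm, part of the between-group difference reflects state at testing.

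**Working it through.** **1. The plan's own figure.** Sample size calculation gives a 50 m difference, SD 80 m, level 0.05 and 80% power; Statistical analyses gives two-sided tests; Randomisation gives 1:1.

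n per arm = 2 × (1.96 + 0.8416)² × 80² / 50² = 2 × 7.849 × 2.56 = 40.2, rounded up to 41, so 82 in total. This matches the article.

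Power at 41 per arm = Φ(50 / (80 × √(2/41)) − 1.96) = Φ(2.83 − 1.96) = 80.8% (79.8% by t-test). The sample size arithmetic is not at issue, but the design has little slack. All figures below use the planning level of 0.05.

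**2. Does the means deliver the end?**

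- End: same medication level, and on-phase, at all three tests.
- Means: approximately the same clock time, as an aim.
- Needed link: intake times and regimen unchanged between visits.
- What the article says about the link: the stay includes follow-up on medication, and medication is registered again later so that change can be assessed.

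The link is not secured, so the means can help but cannot ensure the end.

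**3. Size if the off share is the same in both arms.** The documents give neither the share of tests taken off (q) nor the loss in metres when off (d). Both are assumptions. I also assume that the SD of 80 m does not already contain this variation; if it does, the loss is smaller.

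Added variance on a single-visit score = q(1 − q)d², so SD = √(6400 + q(1 − q)d²).

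| q | d (m) | Added variance (m²) | SD (m) | Power at 41 per arm | n per arm for 80% |
|---|---|---|---|---|---|
| 0 | – | 0 | 80.0 | 80.8% | 41 |
| 10% | 30 | 81 | 80.5 | 80.3% | 41 |
| 20% | 30 | 144 | 80.9 | 79.9% | 42 |
| 10% | 50 | 225 | 81.4 | 79.4% | 42 |
| 20% | 50 | 400 | 82.5 | 78.4% | 43 |
| 30% | 100 | 2100 | 92.2 | 69.0% | 54 |

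If 80 m is instead read as the SD of a change score, and state is independent at the two visits, the added variance doubles to 2q(1 − q)d²:

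- q = 10%, d = 30 m: SD 81.0, power 79.8%.
- q = 20%, d = 50 m: SD 84.9, power 76.1%, 46 per arm.
- q = 30%, d = 100 m: SD 103.0, power 59.4%, 67 per arm.

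These are guides from a two-group comparison of means. They are not the power of the planned mixed model.

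**4. Size if the off share differs by arm.** With equal shares the expected loss, q × d, cancels between arms. Otherwise bias = (difference in q) × d. For a difference of 5 to 20 percentage points:

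- d = 30 m: 1.5 to 6 m
- d = 50 m: 2.5 to 10 m
- d = 100 m: 5 to 20 m

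The target difference is 50 m.

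**The case against.** The strongest reply is that the sentence states an aim and its reason, not a guarantee. The authors name the on-phase as the target and try to standardise towards it. A journal article need not carry test-form detail, and a fuller protocol or assessor manual may already time tests by medication intake. Medication is registered again at follow-up, which allows a partial check. Both randomised arms share the residential baseline, the journey, the disease course and one blinded assessor.

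Much of this stands. That the article does not mention recording intake time or on/off state is not in itself a fault, and one cannot conclude that state will be unrecoverable. The shared procedure means that noise, not bias, is the expected result. What does not stand is the step from clock time to *ensure*: the article states both the rule and its purpose, and the rule does not secure the purpose. A medication list shows what is taken, not when it was last taken or the participant's state at the walk.

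Four stronger readings are tempting and go beyond the documents:

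- *That the 6MWT does mix state with capacity.* No rate of fluctuation or off-state testing is given for this Hoehn and Yahr 1–3 sample.
- *That the protocol expects medication to change.* It plans to detect change, which is less.
- *That travel delays tests.* The 2.5 h is an eligibility limit, and no delay is described.
- *That the comparison is biased.* Routes specific to the intervention arm exist: medication may be raised in the calls (Monthly tele-follow-up by a PT), and the Background says that nutrition can influence how well PD drugs work. But the physiotherapist is described as advising from guidelines or referring onward. Nothing shows that medication state shifts more in one arm.

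**Conclusion.** The concern holds as a limited point about measurement of the primary outcome. An approximate match on clock time cannot ensure the same medication level and on-phase across a residential baseline and visits three and six months later, so on/off state can add noise to the 6MWT. The size is unknown.

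Under small to moderate assumptions the cost is slight: roughly one to two percentage points of power on a single-visit score, and up to about five on a change score. Falls to 69% or 59% need 30% of tests off and a 100 m loss together. Bias arises only if the off share differs by arm. It would then be between 1.5 and 20 m across the assumed range, and no such difference is shown. The point deserves action because the remedy is cheap and the outcome is primary, not because harm has been demonstrated.

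**What to change.** In Assessment and blinding:

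1. Book each follow-up test at the same interval after the participant's usual PD medication intake as at baseline, with clock time as a secondary guide. This moves the appointment, not anyone's medication.
2. Just before the 6MWT, at every visit and in both arms, record the time of last intake and the participant's reported on/off state.
3. Replace *ensure* with *help to ensure*.

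In Statistical analyses: keep all randomised participants in the primary analysis whatever their recorded state. Tabulate state and time since intake by arm and visit, and use them in a supportive sensitivity analysis. Add the caveat that state is measured after randomisation and reported by participants who know their allocation.

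Two further steps should be avoided. Repeating the test when a participant reports being off would make remeasurement of the primary outcome depend on unblinded self-report. Treating an analysis of on-state tests alone as a clean comparison would select on a post-randomisation variable.

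Cost: two extra fields on the test form and less flexible booking. An equal interval does not guarantee an equal level if the regimen has changed, which is why state is recorded as well. Enrolment began in March 2021 and was planned to finish around January 2023, so baselines already taken cannot be recovered. For those participants, recording at the remaining visits and a stated limitation are what is left, unless intake time was noted elsewhere.
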